# 3.0 STUDY DESIGN

This study will use a prospective randomized controlled group design to examine the effectiveness of a six-week yoga-based stress reduction intervention on perceived stress of allogeneic HSCT caregivers (Figures 2, 3). Subjects will be accrued to this protocol once they have been identified and are serving as a primary caregiver (defined as ACTIVE caregiver) for an individual planning to undergo an allogeneic HSCT at the Clinical Center, NIH. The patient and caregiver(s) will be approached for participation before the patient starts their transplant conditioning.

All participants will receive usual care education (UCE), which includes transplant specific information for the recipient and the caregiver, as well as caregiver resources. After study enrollment, caregiver subjects will be randomized to either the control group or the intervention group. A permuted block randomization with allocation ratio of 1:1 will be performed by the study statistician. All participants will meet 1:1 with a study investigator to review the UCE materials. Participants in the intervention group will also receive an audio recording of a 20 minute yoga-based stress reduction intervention, as well as instructions on how to complete the intervention; they will be asked to practice the twenty minute audio file daily for the six weeks of the intervention. The six-week length of the intervention, as well as the 20 minute time of the audio file, was selected based upon the length of similar interventions in other caregiver populations, with interventions ranging between four to ten weeks [^37^](#_ENREF_37)^,^[^43^](#_ENREF_43). All study visits will be scheduled around the HSCT recipient’s schedule and visits to minimize burden for the caregiver. The initial visit for all participants will occur prior to the patient’s initial discharge from the hospital and within 7 days of the HSCT infusion (Day 0+7). Subjects in the intervention group will receive a brief phone call at weeks two and four (+/- 7 days) to assess progress and to record practice. All subjects will participate in an exit interview at week six (+/- 7 days). Study questionnaires will be administered to all subjects at baseline and again at week six (+/- 7 days). Completion will take approximately 20 minutes through a web-based system. If the electronic system is unavailable, a hard copy of the questionnaires will be available for completion. Caregivers in either group who complete baseline assessments but are no longer able to return to the clinical center for their week 6 study visit will be given the option to complete the week 6 questionnaires electronically.

## Figure 2. Participant Flow Progress

##
[figure not shown]

## Figure 3: Study Plan

| Pre-HSCT Cell Infusion (D-0-) | | | Post Transplant Phase | | |
| --- | --- | --- | --- | --- | --- |
| **Time Point** | Baseline Visit & Randomization  (D-0- to +7 days after) | | WK  2  (+/-7 days) | WK  4  (+/-7 days) | WK  6  (+/-7 days) |
|  | Control  Group | Intervention Group | Intervention Group | Intervention Group | All participants |
| Study Activities | | | | | |
| Outpatient Registration | X^a^ | X^a^ |  |  |  |
| Clinical Assessment | X | X |  |  |  |
| Laboratory Samples | X | X |  |  | X |
| Phone call follow-up |  |  | X | X |  |
| Exit Interview |  |  |  |  | X |
| Participant-Reported Psychological & Outcome Measures | | | | | |
| CRA | X | X |  |  | X |
| HPLP-II | X | X |  |  | X |
| PROMIS Measures  Anxiety**  Applied Cognition – General Concerns**  Depression** | X | X |  |  | X |
| NIH Toolbox/Neuro QOL Measures  Loneliness Short Form  Self-Efficacy**  Perceived Stress **  Positive Affect & Well-being | X | X |  |  | X |
| PSQI | X | X |  |  | X |
| MINDFULNESS | X | X |  |  | X |
| MFSI-SF | X | X |  |  | X |
| Demographic Interview | X | X |  |  | X |
| Practice Diary |  | Daily^b^ | | | |
| Clinician Collected Case Report Forms | | | | | |
| Care Recipient Disease & Treatment Characteristics | X | X |  |  | X |

*Note*; CGs: Caregivers; Caregiver Reaction Assessment; HPLP-II: Health Promoting Lifestyle Profile II; PSQI: Pittsburgh Sleep Quality Index; MFSI-SF: Multidimensional Fatigue Symptom Inventory- Short Form; ^a^ Unless previously completed. ^b^ for Intervention Group only; **indicates measure will be administered by computer adaptive test (CAT).

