All caregivers will attend the usual care group education provided at the Clinical Center for transplant caregivers. Caregivers randomized to the intervention group will be scheduled for one session with study personnel to receive a 20 minute audio file of gentle chair yoga poses and guided breath awareness, as well as instructions for performing them, and they will be asked to practice daily. Data, in the form of web-based questionnaires, as well as a physical assessment, demographic interview and blood work will be collected from all study participants at baseline (at or near the time of HSCT) and again at the end of the six-week intervention. There will be no long-term follow-up after the intervention period. Questionnaires include: Caregiver Reaction Assessment, Health-Promoting Lifestyle Profile II, Pittsburgh Sleep Quality Index, Freiburg Mindfulness Scale, PROMIS measures of anxiety, applied cognition, depression, positive affect and well-being, Multidimensional Fatigue Symptom Inventory- Short Form, and NIH Toolbox measures of loneliness, self-efficacy, and perceived stress. Subjects will participate in an exit interview at the end of the study and the interventionist will complete a log, based on subject diaries, that tracks subject practice, and discrepancy between planned and actual session date and time. Quantitative analysis techniques will be used in this study.

Table of Contents

[1.0 STUDY OBJECTIVES & RESEARCH HYPOTHESES 3](#_Toc393800853)

[1.1 Study Objectives & Hypotheses 3](#_Toc393800854)

[1.1.1 Primary Objectives & Hypotheses 3](#_Toc393800855)

[1.2.1 Exploratory Objectives 3](#_Toc393800856)

[2.0 BACKGROUND 3](#_Toc393800857)

[2.1 Stress reduction interventions 6](#_Toc393800858)

[2.2 Scientific Justification 7](#_Toc393800859)

[3.0 STUDY DESIGN 10](#_Toc393800860)

[Figure 2. Participant Flow Progress 11](#_Toc393800861)

[Figure 3: Study Plan 12](#_Toc393800862)

[3.1 Usual Care Education (UCE) 12](#_Toc393800863)

[3.2 Experimental Intervention – Stress reduction intervention 13](#_Toc393800864)

[4.0 ELIGIBILITY ASSESSMENT 14](#_Toc393800865)

[4. 1 Inclusion Criteria 14](#_Toc393800866)

[4.2 Exclusion criteria 14](#_Toc393800867)

[5.0 METHODS 15](#_Toc393800868)

[5.1 Questionnaires: 15](#_Toc393800869)

[5.2 Demographic Interview 18](#_Toc393800870)

[5.3 RESEARCH PARTICIPANT/PATIENT DATA 18](#_Toc393800871)

[5.4 Clinical and Laboratory Assessments 18](#_Toc393800872)

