## Exploratory Objectives

- - - 1. To examine whether HSCT caregivers participating in a stress reduction intervention demonstrate improvement in certain individual factors (self-efficacy, burden, and mindfulness), psychosocial factors (stress, anxiety, depression, loneliness, positive affect and well-being), behaviors (health behaviors) and symptoms (sleep, fatigue, depression, and cognitive impairment) compared with HSCT caregivers in the control group.
      2. To examine whether HSCT caregivers participating in a stress reduction intervention demonstrate improvement in physiological markers of stress (serum cortisol) and clinical (blood pressure, waist circumference, body weight) and biomarkers of inflammation and cardiometabolic disease (lipids profiles, fasting blood glucose, insulin, IL6, TNF-alpha, hs-CRP) compared with HSCT caregivers in the control group.
      3. To examine whether the amount of yoga practiced by HSCT caregivers in the intervention group contributes to improvement in individual factors, psychosocial factors, behaviors, symptoms, as well as physiological markers of stress and clinical and biomarkers of inflammation and cardiometabolic disease.
      4. To characterize subjects with a significant change in perceived stress or other study outcomes (ie: sleep disturbance, depression, anxiety, loneliness) following the intervention, to generate possible hypotheses for future research.

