## 5.4 Clinical and Laboratory Assessments

**5.4.1 Clinical Assessments**

A complete medical history, physical exam and review of current medications, smoking and alcohol consumption, measurement of height, weight, blood pressure, heart rate, and waist circumference. Participants will be weighed in light clothing without shoes to the nearest 0.1 kg and their heights, in centimeters (cm). Body mass index (BMI) will be calculated using the following calculation:

$$\text{BMI=weight}\frac{\text{kg}}{\left[ \text{height }\left( \text{cm} \right) \right]\text{2}}$$

Waist circumference will be measured at the level of the umbilicus with the participant in mid-expiratory position. Blood pressure, measured by Dinamap^®^ Pro 100-400v2 electronic blood pressure machine or by manual sphygmomanometer on either the right or left upper arm of the participant following a 5-minute rest period in a sitting position. Clinic staff obtaining measurements on study participants will be educated on the techniques to obtain measurements for this study.

The presence of metabolic syndrome will be determined based on the NCEP ATP III [^48^](#_ENREF_48). Subjects will be categorized as ‘positive’ if three or more of the following are present: hyperglycemia (fasting blood glucose ≥ 110 mg/dL), hypertension (BP≥130/85 mmHg), hypertriglyceridemia (triglycerides>150 mg/dL), low High-Density Lipoprotein Cholesterol (HDL<40 mg/dL in men and <50 mg/dL in women), and waist circumference >40 inches in men and >35 inches in women. If three or more are not present, subjects will be categorized as ‘negative’ relative to metabolic syndrome.

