## 10.4 Research Subject Compensation

Enrolled subjects will be compensated for inconveniences based on guidelines for NIH Research Participant compensation. Research subjects will receive $15 for each blood sample and $40 for each outpatient visit (registration, H&P and/or clinic follow-ups). A study completion bonus of $50 will be offered for completing **all** study procedures including all clinic visits, laboratory samples and questionnaires completion, for a maximum compensation of $170 for participation. A maximum of no more than 550 mL of blood in an eight week period will be drawn.

An enrolled subject could therefore receive:

1^st^ visit $55 (registration, H&P, collection of blood, surveys)

2-Telephone follow-ups $10 (subjects in intervention group only)

2^nd^ visit $55 (collection of blood, clinic visit, surveys)

Bonus $50 (for completing **all** study procedures)

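### Figure 3 schedules the clinical assessment at baseline only, contradicting the precis, the second exploratory objective and section 6.2, which need blood pressure, waist circumference and weight at week 6 as well

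*Protocol*

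**What the plan says.** In Figure 3 of the protocol, the clinical assessment row reads "Clinical Assessment | X | X": one mark for the control group and one for the intervention group at baseline, and nothing at weeks 2, 4 or 6. The next row begins the same way, "Laboratory Samples | X | X", but also carries a mark in the week-6 column for all participants.

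Section 5.4.1 says what the clinical assessment contains. Besides history, examination and medication review, it includes "measurement of height, weight, blood pressure, heart rate, and waist circumference". It does not say when these are taken.

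The precis gives a timing. It says that a "physical assessment, demographic interview and blood work will be collected from all study participants at baseline", and the full timing phrase in that sentence is "at baseline (at or near the time of HSCT) and again at the end of the six-week intervention".

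The second exploratory objective asks whether the intervention group improves, relative to control, in physiological stress markers and in "clinical (blood pressure, waist circumference, body weight) and biomarkers of inflammation and cardiometabolic disease". The third relates the amount of yoga practised to the same clinical markers.

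Section 6.2 describes all variables at both time points and analyses the exploratory outcomes by linear mixed models. Section 8.1 says that data are collected as laid out in Figures 2 and 3. Section 10.4 describes the second paid visit as "visit $55 (collection of blood, clinic visit, surveys"; the first-visit line includes a history and physical, and the second does not.

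**The concern.** Comparing the arms on improvement needs a value after baseline. The schedule of assessments, to which section 8.1 points for data collection, provides none for blood pressure, waist circumference or weight. The precis, the objectives and the analysis section all presuppose one. A team working from Figure 3 could omit these measurements at week 6 and be following the protocol; a team working from the precis would take them. Values not taken within the week-6 window cannot be recovered afterwards, and no analysis plan can repair that.

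**Working it through.** No sample size, power or error rate enters here. The check sets the passages on timing side by side.

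1. **Is the blank cell deliberate or a slip in the table?** Twelve rows of Figure 3 are marked at baseline for both groups: registration, clinical assessment, laboratory samples, seven questionnaire rows, the demographic interview and the care-recipient form. Ten of the twelve are also marked at week 6. The two that are not are registration, which is naturally done once, and the clinical assessment. So the table does mark repeats where it intends them. The clinical assessment row has the same number of cells as its neighbours, so a mark shifted in text extraction is unlikely, though it cannot be fully excluded.

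2. **What does each place imply for blood pressure, waist circumference and weight at week 6?**

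| Place in the protocol | Week-6 measurement? |
| --- | --- |
| Figure 3 | No |
| Precis | Yes, as part of the physical assessment |
| Exploratory objectives 2 and 3 | Required |
| Section 6.2 | Expected (both time points) |
| Section 5.4.1 | Timing not stated |
| Section 10.4, second visit | Undetermined |
| Section 8.1 | Refers to Figures 2 and 3 |
| Figure 2 | Not shown |

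3. **Does the payment section decide it?** No. Section 10.4 pays $15 per blood sample and $40 per outpatient visit, and $15 + $40 = $55 for both the first and the second visit, so the amounts do not distinguish them. The second line lists a clinic visit separately from blood collection and surveys, which could cover these measurements, but it does not say so.

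4. **Is there another route to the data?** Section 3.0 offers caregivers who cannot return at week 6 electronic completion of the questionnaires only. That does not supply physical measurements.

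5. **Consequence under each reading.** Under Figure 3, each of the three outcomes has 0 post-baseline values in either arm, so no intervention effect on it can be estimated. Under the precis, both time points exist and the planned mixed models can be fitted. Perceived stress is marked at baseline and week 6 in Figure 3, so the primary analysis is the same either way.

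**The case against.** The strongest reply is that the design is clear and only the table is wrong. The precis plans a second physical assessment, section 6.2 assumes two time points, section 10.4 pays for a week-6 clinic visit, and one blank cell stands against them. Because section 5.4.1 opens with a full history and examination, the baseline-only row may refer to that complete work-up, with simple measurements repeated at week 6. Appendix B mentions a manual of procedures and trained clinic staff, so Figure 3 need not be the only working document. Figure 2, which section 8.1 names alongside Figure 3, is not shown and might list week-6 measures.

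Much of this stands. A reader might infer that the objective on blood pressure, waist circumference and weight cannot be answered at all. The documents do not support that, because the precis plans the second assessment. Nor do they establish that the values will be lost; that depends on Figure 3 being followed over the precis.

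The reply does not remove the contradiction. No passage says that the row means only the full work-up. The manual is not part of the document, and if Figure 2 did show a week-6 assessment, it too would conflict with Figure 3.

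**Conclusion.** The protocol contradicts itself on whether blood pressure, waist circumference and weight are measured at week 6, and nothing in the text shown resolves it. If Figure 3 is followed, three exploratory outcomes have no post-baseline value and their between-arm comparison cannot be made; if the precis is followed, nothing is lost. The conclusion assumes that the table was extracted correctly and is limited by the absence of Figure 2. This is more than a clerical matter because section 8.1 directs data collection to the figures, but it affects exploratory outcomes only.

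Two further inferences go beyond the text:

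- **A guaranteed null result.** A reader might argue that last observation carried forward would copy baseline to week 6 and make every change zero. Section 6.2 states that rule in the paragraph on the primary analysis and does not repeat it for the exploratory outcomes. The argument would also require imputing a variable that was never measured at follow-up.
- **Loss of week-6 metabolic syndrome status.** Blood pressure and waist circumference are two of the five components in section 5.4.1. But the second exploratory objective does not name metabolic syndrome status, section 5.4.1 sets no week-6 classification, and section 2.2 speaks only of components of the syndrome.

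**What to change.** Reconcile the passages in one of two ways.

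- **If week-6 measurement is intended:** mark weight, blood pressure and waist circumference in the week-6 column for all participants in Figure 3. If the full history and examination is to stay at baseline only, give these measurements their own row. State in section 5.4.1 that they are taken at baseline and week 6, name them in the second-visit line of section 10.4, and check that Figure 2 agrees.
- **If it is not intended:** remove these outcomes from the exploratory objectives, including the practice-amount objective, and correct the precis.

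The first option costs a wording amendment and a few minutes at a week-6 visit already planned for the blood draw. The second costs no measurement time but gives up the three outcomes.

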## 3.1 Usual Care Education (UCE)

Participants who are enrolled in allogeneic HSCT research protocols at the Clinical Center receive information from a variety of sources and individuals. Early in the transplant process an institute representative (coordinator) will provide institutional information along with an overview of HSCT from organizations such as the Leukemia and Lymphoma Society, The National Marrow Donor Foundation and Be the Match. Prior to in-patient admission for transplant conditioning, patients and their caregivers receive information specific to the transplant process, complications, monitoring and management, and general tips on caregiving including caregiver specific electronic resources ([www.cc.nih.gov/wecare](http://www.cc.nih.gov/wecare)). Additional information such as medication education is provided to each patient during their admission by the various providers (RN, Pharmacist) involved in their care.

Discharge from the in-patient unit is based on the patient’s clinical recovery (blood counts, nutrition, and infection) as well as the capacity of the patient and the caregiver to manage the complex routine. This includes venous access device (central line care), safe food preparation, transportation, infection prevention strategies, and medication administration. As discharge from the hospital approaches, patients and caregivers are provided with a Transplant Discharge Class to review additional complications and outpatient expectations. In addition, information regarding their new ‘routine’ in the outpatient area is provided. All the documents provided as a component of usual care education are considered expert information. If participants are unable to attend the discharge class, they are given the educational information presented in the class individually by inpatient nursing staff prior to discharge. Receipt of UCE will be documented by the study team.

## 3.2 Experimental Intervention – Stress reduction intervention Appendix A

After baseline measures have been obtained and subjects have been randomized into the intervention and control groups, subjects in the intervention group will meet with the interventionist for approximately 20 minutes to go over instructions for performing the gentle chair yoga and breath work that they will be asked to perform daily using a 20-minute audio recording that they will receive in this meeting. The stress reduction intervention (Appendix A) will be provided to subjects by a trained interventionist. The intervention will be delivered by [name], RN, who is a registered nurse with a master’s degree in psychiatric-mental health nursing, and is a certified Iyengar Yoga Instructor, or by study staff who have received training by [name]. Participants will then practice the recording one time under the supervision of study staff.

The audio recording was developed by Advanced Iyengar Yoga Instructor, [name], who has over 35 years of experience teaching yoga and has recorded numerous audiotapes of yoga for home practice. [name] worked with [name] to develop the intervention, based upon [name] years of teaching experience, as well as the research literature that shows the effectiveness of similar yogic breathing exercises in reducing levels of perceived stress [^53^](#_ENREF_53) and similar chair-based yoga interventions in improving levels of depression, anxiety, quality of life, and well-being in elderly populations [^54^](#_ENREF_54)^,^[^55^](#_ENREF_55). The 20-minute audio recording will lead participants through a series of gentle stretching and breathing exercises [^53-55^](#_ENREF_53). The first few poses will be performed standing, using the wall for support. The remainder of the audio file will consist of gentle seated yoga poses (stretches and twists) that are performed in a chair, as well as guided breathing exercises that focus primarily on slowing and quieting the inhalations and exhalations.

Small (<5 GB) audio players will be purchased and given to subjects in the intervention group. These devices will be preloaded with the 20-minute audio file of the stress reduction intervention. Upon completion of the study, control group subjects will also receive an audio player with the intervention recording and no subjects will be asked to return their device.

Subjects in the intervention group will be asked to practice the 20-minute audio recording daily. They will be asked to maintain a diary of practice, and study staff will contact them by phone at weeks two and four for a brief call to answer questions and to record practice days (this same information will be obtained in person at the exit interview). Subjects in the control group will be offered a complementary audio file of the same stress reduction intervention received by the intervention group, along with written instructions regarding how to perform the exercises, at the conclusion of their participation in the study.

The PI will take several measures to ensure the integrity and consistency of the intervention across subjects, and these measures are described in the Treatment Fidelity document in Appendix B. The interventionist is a certified Iyengar yoga instructor, and received training for the stress reduction component of the intervention from Advanced Iyengar Yoga instructor [name], who created the practice audio files for study participants. Interventionists will review instructions for completing the gentle chair yoga poses and breathing exercises with subjects in the intervention group, and will have all subjects demonstrate understanding of how to perform these in a 1:1 initial session. Lastly, random audits of the intervention delivery by the study team through observation will assure that the intervention is being delivered as designed. In addition to practice diaries to record the amount of practice performed by the intervention group, study staff will contact members of the intervention group every two weeks during the intervention to verify amount of practice. Study staff will maintain an electronic log of all in-person and telephone contact with subjects and the documentation will be reviewed by the study team monthly when subjects are actively enrolled.

